### Task 2 – Engagement in a Peer Planning Approach to Build Capacity for AHC Model Navigation Activities

The peer planning approach includes stakeholder committee meetings and a two-meeting planning session. The meetings include stakeholders from the research team; bridge organization and clinical delivery site (CDS) staff including organizational leadership, AHC managers, and AHC navigators; and any other key partners in AHC implementation. The stakeholder committee will meet four times over a three-month period with two meetings before the planning session to assess current AHC Model activities and two meetings after the planning session to finalize the QI protocol. Bi-weekly or monthly meetings will be conducted during the implementation of the QI protocol with the committee's discretion. Due to the outbreak of the novel coronavirus in the U.S. in early 2020, each meeting will be conducted over videoconference (i.e., WebEx) in addition to being audio-recorded. Among the research team, there will be at least one facilitator to guide discussion, one co-facilitator to assist with discussion, time management, and note taking, and one note taker to capture a detailed account of each meeting.

In the first stakeholder committee meeting, the research team will review the SPAN protocol and memorandums of understanding (MOUs), roles and responsibilities for committee members will be assigned, a communication plan will be created, and all committee members will agree on the goals for stakeholder meetings. In the second stakeholder meeting, baseline navigation data collection to identify if current navigation milestones are being met by bridge organizations and findings from the assessment (Task 1) will be discussed. The baseline navigation data will be collected from monthly monitoring reports each bridge organization must provide to CMMI. Before the meeting, the research team will present the process maps of the bridge organization's current site activities based on the assessment findings. Bridge organization and CDS stakeholders will review and provide feedback on the process maps during the meeting. During the first planning session meeting, the research team will review and make any additional modifications to the process map(s) created in the stakeholder meeting. Based on the assessment and process mapping, staff will align current implementation strategies with best practices based on the ERIC implementation strategies for multi-component interventions (34). In the second planning session meeting, an IM planning session will be held to focus on areas where QI could be helpful for the AHC site's current implementation approach and focus on prioritization of AHC implementation performance objectives and determinants. The aim of the second planning meeting is to identify between two and four modifiable determinants to be mapped to specific ERIC implementation strategies for QI. The staff will use these strategies to create the QI protocol, revised standard operating procedures (SOPs), implementation plan, navigation milestone plan, and other relevant QI documents at the third and fourth stakeholder meetings.

### Task 3 – Co-creation of a Quality Improvement (QI) Protocol for AHC Model Navigation Activities

Following peer planning, a third stakeholder meeting will be held with each bridge organization to develop a quality improvement (QI) protocol and to update QI documents for AHC Model implementation at the CDS. The QI protocol allows each bridge organization to demonstrate AHC navigation implementation achievement and determine short term impact on milestones. The protocol will build on activities and data collected in Tasks 1 and 2. The fourth stakeholder meeting will focus on key components of a QI protocol and completion of a written QI protocol. As shown in Table 2, the QI protocol will be completed using the Quality Improvement (QI) Bridge Organization Team Charter Template. The template was adapted from QI protocol charters developed by the Agency for Healthcare Research and Quality (AHRQ) Quality Indicators Toolkit (44), Institute for Healthcare Improvement (IHI) (45), and CMS Medicare Quality Assurance and Performance Improvement programs (46). The purpose of the template is to describe the stakeholder committee roles, QI protocol aims, scope and timeline, protocol implementation strategies, and change management strategies (e.g., how to measure QI protocol success). Upon review and approval by each bridge organization, the protocol will be sent to CMMI for review and approval. CMMI leadership and program officers will review the protocol to ensure there is no overlap with existing Model activities or budgetary fund allocation. Upon approval by CMMI, each bridge organization will complete the Quality Improvement Protocol Readiness Assessment Checklist outlined in Table 3 (47). Upon expressing readiness to implement the QI protocol, bridge organizations staff will be assigned to the new protocol, budgetary funds will be released to support implementation by the bridge organization and implementation will begin. A minimum of two additional stakeholder meetings will be held during QI protocol implementation to provide facilitation, support, and ongoing assistance to each bridge organization.

**Table 2 T2:** Quality improvement bridge organization team charter template.

Bridge Organization Name:
QI Protocol Aim:
Bridge Organization QI Protocol Sponsor:
Protocol Background:
QI Protocol Scope:
QI Protocol Implementation Strategies:
QI Protocol Change Management Strategies (take from planning meetings):
Estimated Date for Start and End of QI Protocol:
Team Meeting Frequency during QI Protocol:
Team Members Participating:
Notes:

*Adapted from (44–46)*.

**Table 3 T3:** Quality improvement protocol readiness assessment checklist.

**No**.	**Pre-Implementation Task**	**Yes**	**No**	**If no, why not?**	**Documentation**

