#### Evaluation of the QI Intervention

The evaluation of the QI intervention will be conducted by evaluators not directly involved in the delivery of the QI intervention. Process evaluation will assess implementation fidelity, and perceptions of those delivering and receiving the QI protocol. Implementation fidelity refers to the extent to which the planned QI protocol and revised standard operating procedures are implemented as planned. For the process evaluation, data will be collected in document review and semi-structured interviews with staff responsible for implementing the QI intervention. The evaluator will review the QI protocol, revised standard operating procedures, and navigation milestone quarterly reports submitted to CMMI and any other relevant QI documents. Coupled with the document review, semi-structured interviews with staff will be conducted to establish the current activities. Staff interviews will also assess the perceptions of the peer planning approach and QI protocol implementation. The staff interviews will be guided by the CFIR constructs used in Task 1 in order to assess staff perceptions and experiences of the QI process.

For the outcome evaluation, the methods and analysis of the document review and semi-structured interviews will reflect methods outlined in Task 1. Semi-structured interviews with the protocol staff will be used to assess progress toward intended outcomes of the QI intervention (e.g., staff satisfaction, increased self-efficacy in QI delivery). A keyword thematic analysis will be conducted to develop common themes to compare planned and current AHC activities. The themes will be considered in terms of their relationships to one another within the QI intervention and AHC navigation implementation. The evaluation team will create a coding structure to develop common themes in order to compare planned and current activities in addition to perceptions of peer planning, AHC navigation implementation, and QI protocol, as appropriate. A modified conceptual framework for implementation fidelity will be used to identify potential moderators (e.g., recruitment, participant responsiveness, comprehensiveness of policy description) to successful implementation (48). The outcomes from the QI protocols (described below) will also be used as metrics of success for the larger QI intervention.

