#### Evaluation of the QI Protocols

The evaluation of the QI protocols will be completed by the research team in collaboration with the staff implementing the QI protocol at each bridge organization and the CDS. The staff implementing the QI protocol will evaluate their own protocol in order to provide the staff with the tools and skills needed to conduct and assess future QI protocols (capacity building). Implementation fidelity will be assessed using similar metrics and methods as described for the QI intervention evaluation (see above description). During the planning process for the QI protocol, the research team staff will work with each organization to identify specific outcomes they want to focus on through their QI protocol. The QI protocols identified during this planning phase will be used to inform the data collected for both the process and outcome evaluation. Outcome measures will be based on data generated from weekly data files submitted to CMMI by each bridge organization as required per the Model terms and conditions of award. Weekly files are converted to CMS records and available through the bridge organization monthly monitoring report in the AHC Portal. We anticipate a period of 6 months of intervention data will be available for each site for comparative purposes. Each bridge organization will extract data from their monthly monitoring report for the previous 12 months, which will serve as the baseline data period. Data extracted for each bridge organization will vary per site and protocol based on the staff identified QI protocol and patient interviews but examples include: the unique number of beneficiaries who accepted navigation, the number of core needs resolved from navigation cases, and the number of closed navigation cases with no core needs met. Data for the intervention period (implementation of the QI protocol) will be extracted using the same report and measures. Descriptive statistics [mean, median, range, interquartile range (IQR)] will be calculated for each time period for all measures and compared across time using parametric or non-parametric statistics as appropriate.

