## Discussion

It is expected that this research will increase understanding of how a QI intervention through a structured peer planning approach can provide successful TA for improving the AHC Model.

First, despite this study protocol being limited to the U.S. health system, the AHC Model was largely developed from similar social prescription interventions in other countries (2). Due to our focus on the implementation of the Model in the US, our approach may be limited or need adaptation prior to use in other countries with differing health systems. Future adaption of this protocol, particularly with those participating in social prescribing interventions in the U.S., should consider these as potential enhancements in intervention development and QI methods (2). Second, while the bridge organizations participating in the QI intervention reflect a diversity of geographic locations, beneficiary demographics, size, and type (e.g., county governments, hospitals, universities, and health departments), the process for determining bridge organizations used in this study was an informal and subjective process. Future implementers are encouraged to use objective measures with an implementation science basis, to assess organizational needs and site readiness. The inclusion criteria for the QI intervention was also limited to urban or suburban sites as outlined by the funder. Additional research might be needed to explore the implementation of this protocol with rural sites. A strength of the proposed approach in this protocol is our ability to evaluate the impact of TA on the AHC Model. Third, the current study will develop and test a potential conceptual framework for a QI intervention by linking three implementation science frameworks. Using an implementation science framework can help ensure the adoption and sustainability of structured peer planning and TA interventions in both bridge organizations and in other settings (27). The framework will guide assessment and implementation of current AHC Model activities, QI intervention, the peer planning approach, and QI protocols. The TA and peer planning literature lacks an organizing, conceptual framework. There are limited examples of the application of an organizing framework that uses a locally tailored approach to identify evidence-based determinants and develop strategies to address the determinants. The use of the framework will allow for local tailoring in each Task based on each bridge organization's needs while also providing consistency in implementation across bridge organizations. Next, the findings will describe the implementation of a QI intervention through a peer planning approach with TA over WebEx. As there is limited evidence regarding the implementation of peer planning approaches particularly through remote or off-site TA, this protocol provides a way to further test and understand the impact of off-site TA generally (49). Most studies exploring off-site TA have focused on conference calls and online webinars rather than ongoing, personalized interactions with the TA providers. In the QI intervention, off-site TA will be provided through ongoing, interactive video meetings (WebEx) in addition to interactions through email, phone calls, and *ad hoc* meetings with the TA providers and AHC stakeholders. We will embed internal participatory and interactive engagement structures to ensure off-site TA fidelity and success. Lastly a mixed-methods approach will integrate findings from the evaluation of the QI intervention and each QI protocol providing a greater understanding of the global AHC navigation implementation. We will use a variety of data sources such as interviews with the staff responsible for implementing the QI intervention and recipients of the QI intervention (bridge organization and CDS staff), review of documents, and CMMI navigation milestone quarterly reports. This will increase the validity of the evaluation. The evaluation of the peer planning and TA approach at two different layers is an opportunity to identify possible implementation CFIR moderators and evaluate process and outcome navigation measures. To date, evidence from a multi-layer evaluation of the impact of the peer planning and TA approach is limited.

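### Implementation funds are released and staff assigned in the step that starts each QI protocol, so the before-after change reflects the whole package and cannot be credited to peer planning and TA alone

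*Protocol article*

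**What the plan says.** Task 3 of the protocol article describes what happens after the funder's Innovation Center approves a site's QI protocol and the site completes its readiness checklist: "bridge organizations staff will be assigned to the new protocol, budgetary funds will be released to support implementation by the bridge organization". Implementation begins in the same sentence. Before that, the Innovation Center reviews the protocol to "ensure there is no overlap with existing Model activities or budgetary fund allocation".

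The section on evaluation of the QI protocols sets the comparison. Each site will "extract data from their monthly monitoring report for the previous 12 months, which will serve as the baseline data period". For the later period, "We anticipate a period of 6 months of intervention data will be available for each site for comparative purposes", and "Data for the intervention period (implementation of the QI protocol) will be extracted using the same report and measures". The two periods are compared over time within each site. All five participating organizations receive the intervention, and the article describes no comparison site.

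The result is attributed in four places:

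- The study design text and the title of Task 4 both describe the evaluation as measuring the impact of peer planning and TA.
- The section on evaluation of the QI intervention carries the site results upward: "The outcomes from the QI protocols (described below) will also be used as metrics of success for the larger QI intervention".
- The Discussion says: "A strength of the proposed approach in this protocol is our ability to evaluate the impact of TA on the AHC Model".

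None of these names implementation funding as part of what is evaluated. The limitations in the Discussion and the section on anticipated challenges do not raise it as an alternative explanation.

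**The concern.** The study sets out to learn whether structured peer planning is successful TA, and it offers its approach to TA providers outside the AHC Model. The outcome contrast can support that claim only if peer planning and TA, acting through the QI protocol, are what changed between the two periods. Task 3 shows that money to support implementation also arrives at that point.

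The protocol itself regards resources as relevant: its section on anticipated challenges lists limited time and resources among the barriers. Two of its three example outcomes, beneficiaries accepting navigation and core needs resolved, are counts that could plausibly rise with more resources. If funding contributed to a gain, an organization that copied the meetings without the money should not expect the same result, and nothing in the report would warn it.

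**Working it through.** The article gives no sample size, effect size or other figure for this comparison, so there is nothing to reproduce. The question is whether the planned data could separate the two inputs.

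**Inputs from the protocol article**

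- Sites: 5, all receiving the intervention (SPAN Protocol section).
- Baseline: 12 months; intervention: about 6 months (Evaluation of the QI Protocols).
- The intervention period is the period of QI protocol implementation (same section).
- Funds, staff assignment and implementation start in one step (Task 3).

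**Model.** For site s in month m, let the mean outcome be

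μ(s,m) = a(s) + T·P(s,m) + F·G(s,m)

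Here a(s) is a site effect, P = 1 once the QI protocol is running, and G = 1 once funds are released. T is the effect of planning and TA acting through the QI protocol. F is the effect of the funds.

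**Same start, as the article describes.** There are 5 × (12 + 6) = 90 site-months and 5 + 1 + 1 = 7 columns. P and G are equal in every row, so the design matrix has rank 6 of 7. The data estimate only the sum D = T + F. For an observed change D, T = D − F. If the funds account for a share p of the change, T = (1 − p)·D, which runs from D at p = 0 to zero at p = 1. The article gives nothing from which to set p.

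**Would staggered site starts help?** Assume starts one month apart, with calendar-month effects. The months observed span 22, giving 21 month columns, and 5 + 21 + 2 = 28 columns in all. The rank is 27. Removing the funding column leaves 27 columns with rank 27. Staggering can help with calendar trend but does not separate T from F.

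**What would separate them?** Only a different start for the funds. With an assumed 3-month lag of funding behind the QI protocol, the matrix has full rank, 7 of 7. The article describes no such lag.

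**Timing of the planning meetings.** Most of the peer planning takes place before the funds arrive. This does not rescue the contrast. The analysis uses two periods only, and the QI protocol through which planning is meant to act starts with the funds. The article does not say exactly where the 12 baseline months end, but on any reading the intervention months are those after release of the funds.

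**Are the funds additional?** The check for overlap with existing budget allocations implies that they are. It does not state this outright and gives no amount.

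**The case against.** The strongest reply is that the evaluated intervention is already a package. The article defines the QI intervention as four Tasks, the release of funds sits inside Task 3, and site outcomes are called metrics for the larger QI intervention. On that reading the funds are an input to the intervention and not an external confounder. Components that start together can never be separated in a bundled intervention, and the protocol does not claim to separate them. This largely stands, and it determines the form of the fix: the design need not change. But the article never names funding as a component, and it states its claim for peer planning and TA. A package reading has to be written down to govern the conclusions.

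A reader might infer more than the text supports:

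- **That sites gained navigators or paid hours.** Task 3 says that the organization's staff are assigned, which may mean existing staff given new roles. It does not say that the funds pay for navigation time. A site's strategies come from two to four determinants chosen in planning and need not involve staffing. Any percentage gain from added posts would be conjecture.
- **That resources lie outside the conceptual framework.** The background table of TA phases includes determining and providing resources, the text on the implementation framework mentions organizational resources, and the framework figure is not shown. The supportable statement is only that implementation funding is not named as an evaluated component.
- **That staffing goes unrecorded.** The team charter lists participating members and the readiness checklist asks about implementers. What the article does not describe is a record of staff time or funds.
- **That a gain which vanishes per navigator is not a TA effect.** If a site's own QI strategy is to reassign or add staff, staffing is part of how the intervention works. Dividing it out would remove a genuine effect.

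Staff interviews may explore the role of resources, but they cannot separate it in the quantitative comparison.

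**Conclusion.** The point holds as a mismatch between the contrast and the claim. As described, the before-after change is the effect of peer planning, TA, the QI protocol and the implementation funds together, subject to the usual limits of an uncontrolled comparison. It cannot be credited to peer planning and TA alone. Neither a stable baseline trend nor staggered site starts would change that.

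The conclusion rests on the funds being released when implementation starts, which Task 3 states, and on their being additional to existing Model funding, which the overlap check implies. The size of any funding effect is unknown and could be nil. The documents do not support the stronger conclusion that observed gains would be bought navigator time. The point deserves correction because it changes what the study may conclude and what adopters would take from it.

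**What to change.** 1. In Task 4, define the evaluated intervention as peer planning and TA together with the released implementation funds and assigned staff.
2. Limit the Discussion's claim about evaluating the impact of TA to that package, and list the co-occurring funding as a limitation.
3. Have each site record the funds released and its navigation staff time per month over baseline and intervention. Report both beside the navigation outcomes.
4. If outcomes per full-time equivalent are shown, label them descriptive and secondary, because staffing may be part of a site's QI strategy. They should not decide whether a gain counts as an effect.

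The cost is a small amount of extra recording at five sites, an added table and a narrower claim. The design, data source and comparison stay as they are.
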